**Data collection methods – quantitative**

The MAISHA study schedule is outlined in Figure 3 (adapted from the SPIRIT template [14]). Data are collected at the following time points:

1. Baseline (prior to randomization) – following informed consent procedures, a face-to-face interview is conducted using a structured questionnaire adapted from the WHO Violence Against Women instrument [8]. The MAISHA questionnaire has seven sections which ask the woman about her: household; partner; income; health; attitudes and social norms; relationship (including experiences of violence); childhood; and about her community. The questionnaire has been translated into Swahili (the national language) and interviews are conducted in private by female interviewers trained in interviewing techniques, gender issues, violence and ethical issues related to research on IPV [15].

2. Intervention – during the 20-week intervention period, the following data are collected: attendance, or not, at the MAISHA curriculum sessions – to understand the “dose” of intervention received; and reasons for non-attendance at the MAISHA curriculum sessions – to understand the potential barriers to attendance.

3. 29 months post-randomization – a face-to-face interview is conducted using a structured questionnaire similar to that used at baseline and following the same procedures.

**Data collection methods – qualitative**

A total of 54 in-depth interviews (IDIs) are being conducted with participants. Eighteen women are being purposefully selected from the two study arms to represent women who do and do not report IPV at baseline. A separate team of trained interviewers conduct the IDIs and are blinded as to whether, or not, a woman has reported IPV. Each woman is invited to attend three IDIs – pre-intervention, immediately post-intervention and 24 months post-intervention. The IDIs explore the participants’ life stories and experiences of microfinance, the socio-cultural and structural factors associated with IPV and personal experiences of IPV and its impact on both themselves and their children. For women in the intervention arm, the post-intervention IDIs also explore their views and experiences of the MAISHA curriculum and its impact on their experiences of IPV. Five trial participants from the intervention arm who drop out of the MAISHA curriculum after attending two sessions will be invited to participate in an IDI to explore their reasons for withdrawal from the MAISHA curriculum.

Up to 10 key informant interviews are being conducted with local government and non-governmental organization officials, police, influential community leaders (e.g. religious leaders) and health care professionals. Interviews are conducted pre-intervention and 24 months post-intervention and explore the wider social and political context for IPV.

Twenty-seven focus group discussions (FGDs) are being conducted – comprising nine FGDs at three time points (pre-intervention, immediately post-intervention and 24 months post-intervention). Six FGDs are being conducted with women in the intervention arm and three with women in the control arm. Where possible the same women (approximately 10 per focus group) are asked to attend at all three time points. The FGDs explore experiences of microfinance, the socio-cultural and structural factors associated with IPV. The post-intervention FGDs with women in the intervention arm also explore their views and experiences of the MAISHA curriculum and its impact on their views of IPV.

FGDs are being conducted with the MAISHA curriculum facilitators to explore their views on the curriculum as a whole and on specific modules, the challenges they have experienced when delivering the sessions, and their perspectives on the impact of the MAISHA curriculum.

The photo voices method is being used to enhance understanding of IPV and intimate relationships. A total of nine women (six from the intervention arm and three from the control arm) are invited to take part immediately post-intervention. Participants receive two days training on using a camera and the ethics of taking photographs in the community before being asked to spend one week photographing everyday lives in their community with a focus on healthy relationships. The participants are then interviewed and asked to provide oral narratives of the photographs they have taken.

Participatory observations are being conducted at selected microfinance loan group meetings and at the MAISHA curriculum sessions, ensuring that each session is observed at least once. Social scientists have Informal conversations with study participants to assess their impressions of the curriculum sessions and its immediate impact.

**Data management**

Questionnaire data collected from study participants at baseline and at 29 months post-randomization are recorded directly onto a tablet computer. The questionnaire forms have in-built checks to minimize the level of missing data and to minimize entry of erroneous data. The data recorded on the tablet computer are uploaded to the study database daily and checked for missing and/or erroneous data. Any data queries are sent to the team leader to be resolved with the research assistants conducting the interviews.

Attendance at the MAISHA curriculum sessions and reasons for non-attendance are recorded on paper and entered into the study database following double-entry data procedures. Data are checked for missing and/or erroneous data. Any data queries are sent to the team leader to be resolved with the MAISHA curriculum facilitators.

All IDIs and FGDs are recorded with the participant’s consent. Hand written notes are taken during the participatory observations of the MAISHA curriculum sessions and microfinance loan group meetings. Audio recordings and hand written notes are transcribed and translated from Swahili (the national language) into English. A sample of the transcripts are checked for quality of transcription and translation. Transcripts are imported to the qualitative analysis package NVIVO (QSR International Pty Ltd, Doncaster, Australia). All visual material, including photographs from the photo voices activities, are imported into the same package.

All study data are stored in secure databases with restricted access. Each participant is allocated a unique study identifier. Names and other identifiers are not recorded in the study database. Paper records – e.g. consent forms, tracking forms with names and contact details – are stored securely in locked filing cabinets in secure offices within the study coordinating center at MITU, which has 24-hour security and restricted access.

**Statistical methods**

A detailed statistical analysis plan will be prepared prior to follow-up interviews. Data from the baseline interviews will be used to verify the sample size calculations and to identify differences between clusters. The coefficient of variation across clusters will be calculated based on the reported prevalence of IPV. Data from the baseline quantitative interviews will also be used to identify important predictors for IPV and important health-related outcomes, such as poor mental health.

The primary study analysis will adopt an intention to treat approach, assessing the impact of the intervention on women in the intervention arm at 29 months post-randomization (24 months post-intervention), irrespective of whether or not they received the full “dose” (i.e. 10 sessions) of the MAISHA curriculum. Secondary analyses will be conducted to investigate differences in impact according to the dose of the intervention received.

The primary outcome variable (reported experience of a composite of physical and/or sexual IPV during the past 12 months) will be analyzed in a random intercepts logistic regression model to account for the clustered study design, and adjusted for differences in baseline characteristics where relevant. The analysis will be repeated to examine the secondary outcome variables – reported experience of physical IPV, sexual IPV and emotional/psychological abuse during the past 12 months, attitudes towards the acceptability of IPV and, disclosure of violence to others among women who report having experienced physical and/or sexual IPV during the past 12 months. Multiple imputation will be used to simulate missing outcome data. The imputation model will be informed by empirical patterns in the IPV data at baseline and at follow-up. A sensitivity analysis will be conducted, excluding women who participated in the qualitative sub-study (including IDIs, FGDs and photo voices) on the basis that the additional contact of this sub-sample with the study team, as part of these activities, may impact on the effect of the intervention. The analysis will assess if there is any change in the magnitude of the effect.

Steps have been taken to minimize contamination of the control arm which includes recording women’s attendance at sessions. The potential for direct and indirect contamination of control arm women will be investigated by asking women during follow-up if they attended any of the MAISHA curriculum sessions or if they have discussed any of the sessions with women in the intervention arm.

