**Participant timeline**

Following enrolment into the study, baseline data are collected from women who have consented to take part. Randomization occurs once all women in a block of six microfinance loan groups have completed the baseline interview. The intervention is delivered over 20 weeks (five months) and women in both study arms are then followed up 24 months later, i.e. 29 months post-randomization (Figure 2).

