| Physical IPV ^a^ |  |  |  |  |  |  |  | x |
| Sexual IPV ^a^ |  |  |  |  |  |  |  | x |
| Emotional abuse ^a^ |  |  |  |  |  |  |  | x |
| Attitudes about IPV |  |  |  |  |  |  |  | x |
| Disclosure of IPV to others ^a^ |  |  |  |  |  |  |  | x |
| In-depth interview ^b^ |  |  |  |  |  |  |  | x |
| Focus group discussion ^b^ |  |  |  |  |  |  |  | x |

MF-group based microfinance loan; PGT-participatory gender training; IPV-intimate partner violence;

^a^ Reported experience in past 12 months

^b^ Participants will be random sample of women from control and intervention arms – same women will participate at three time-points

^c^ immediately following completion of the MAISHA curriculum

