**Progress and timelines**

For MAISHA CRT01, recruitment of 66 established formal microfinance loan groups is complete. Of these, 33 groups were randomly allocated to the intervention arm and 33 groups to the control arm. Delivery of the MAISHA curriculum to the 33 groups allocated to the intervention arm is complete. Baseline interviews with participants indicate a prevalence of physical and/or sexual IPV during the past 12 months of 27% (95% confidence interval: 24% to 29%) [17], confirming the assumption made for the sample size calculation of 30% prevalence of physical and/or sexual IPV during the past 12 months. Follow-up of participants for assessment of the primary and secondary outcomes at 24 months post-intervention is almost complete. Data analysis will be conducted from 2018 onwards and the results of the trial disseminated as described above.

For MAISHA CRT02, formation and recruitment of 66 groups of women not engaged in formal group-based microfinance activities is complete. Delivery of the MAISHA curriculum to the 33 groups allocated to the intervention arm is also complete. Follow-up of women for the primary and secondary outcomes will commence in 2018. A separate paper describing the protocol for MAISHA CRT02 has been prepared.

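### The primary model's covariate rule rests on observed baseline differences and does not fix baseline IPV as a covariate; the cost is power, not validity

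*Protocol*

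**What the plan says.** Protocol, Statistical methods: the primary outcome "will be analyzed in a random intercepts logistic regression model to account for the clustered study design". The adjustment rule attached to that model reads "and adjusted for differences in baseline characteristics where relevant". No covariate is named. Neither a difference nor relevance is defined, and the text does not say whether the adjusted or the unadjusted result is primary.

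The obvious covariate is already collected. Under Participant timeline, "baseline data are collected from women who have consented to take part", and a block is randomised only after its baseline interviews are complete. Table 3 schedules physical and sexual IPV at baseline and at month 29, both as "Reported experience in past 12 months". The follow-up questionnaire is similar to the baseline one, and each woman has a unique identifier.

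The same section gives baseline IPV other uses. For missing data, "The imputation model will be informed by empirical patterns in the IPV data at baseline and at follow-up". Separately, "Data from the baseline quantitative interviews will also be used to identify important predictors for IPV", but nothing links those predictors to the primary model. Detail is deferred: "A detailed statistical analysis plan will be prepared prior to follow-up interviews". Analysts will be blinded to allocation.

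**The concern.** Because groups are randomised after baseline, any difference between arms in a baseline characteristic is due to chance. Its observed size does not say whether adjusting for it helps; that depends on how strongly it predicts the outcome. Baseline past-12-month IPV is the same construct as the primary outcome, asked of the same women, so it is the natural candidate. A rule keyed to differences leaves it out when the arms happen to look alike, which is the usual case.

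Two things could be at stake. One is power that needs no further data to obtain. The other is the freedom an undefined relevance condition leaves over which model is reported.

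**Working it through.** **Inputs.** From the protocol's Sample size section: 33 groups per arm; 20 women per group with 10% loss, read here as m = 18 analysed; ICC 0.02; 30% relative reduction; control prevalence 30%. From Progress and timelines: observed baseline prevalence 27%. Assumed: two-sided alpha 0.05; individual baseline to follow-up correlation r = 0.2 to 0.5; correlation c of group effects between the two interviews, 0 to 1. Neither r nor c is in the documents.

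**The plan's own figure.** Design effect = 1 + 17 × 0.02 = 1.34, so effective n per arm = 33 × 18 / 1.34 = 443.3. For 30% against 21%: SE = √[(0.30×0.70 + 0.21×0.79)/443.3] = 0.0291, z = 0.09/0.0291 = 3.09, power = Φ(3.09 − 1.96) ≈ 87%. The protocol states 80%. That figure is reproduced at about 14 women analysed per group, so it is conservative. This is a separate matter and does not affect the point here.

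**Unadjusted power at the observed prevalence.** For 27% against 18.9%: SE = √[(0.27×0.73 + 0.189×0.811)/443.3] = 0.0281, z = 0.081/0.0281 = 2.88, power = Φ(0.92) ≈ 82%.

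**Always adjusting for baseline IPV.** In units of the outcome variance, an unadjusted group mean has variance 0.02 + 0.98/18 = 0.0744. After regression on baseline IPV with slope r (same variance and ICC at both times) it is

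V = 0.02(1 − 2rc + r²) + (0.98/18)(1 − 2rw + r²), with w = (r − 0.02c)/0.98,

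and power = Φ(2.88/√(V/0.0744) − 1.96).

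| r | c = 0: V, power | c = 1: V, power | Simulated range |
|---|---|---|---|
| 0.2 | 0.0730, 82.9% | 0.0654, 86.7% | 82–87% |
| 0.3 | 0.0711, 83.8% | 0.0598, 89.5% | 83–90% |
| 0.4 | 0.0686, 85.1% | 0.0535, 92.5% | 86–93% |

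Formula and simulation (33 + 33 groups of 18) agree to within about a point. Setting c = r reduces V to 0.0744(1 − r²). Power is then 83.4%, 85.3%, 88.0% and 91.3% at r = 0.2, 0.3, 0.4 and 0.5. The equivalent gain in sample, 1/(1 − r²) − 1, is 4%, 10%, 19% and 33%.

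**Adjusting only when baseline IPV differs at p<0.05.** The threshold is an illustration; the protocol gives none. Simulation: 30% against 21%, 66 groups of 18, 10,000 trials per scenario, cluster-level t-test on raw means or on residuals from baseline IPV.

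| r | Unadjusted power | Always adjusted | Triggered | Type I error, triggered | Type I error, better of two |
|---|---|---|---|---|---|
| 0.2 | 88.0% | 89.8% | 88.2% | 4.8% | 6.0% |
| 0.3 | 88.0% | 91.4% | 88.3% | 4.8% | 6.4% |
| 0.4 | 87.5% | 92.8% | 88.0% | 4.6% | 7.0% |
| 0.5 | 88.2% | 95.4% | 89.2% | 4.2% | 7.2% |

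The triggered rule gains about one point or less. At 27% prevalence it likewise gains about one point or less.

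**The case against.** The strongest reply is that covariates are normally named in the SAP, which is not at hand, and that the relevance condition could mean prognostic relevance. In part this stands: the SAP may well name baseline IPV, and it cannot be said that the final analysis omits it. But the protocol is not merely silent. The criterion it writes down is baseline differences, and an SAP that follows it starts from the wrong one.

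Four stronger readings are tempting, and the documents do not support them.

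- *The rule invalidates the test.* A strict imbalance rule holds type I error. Inflation needs someone to pick the better of two results, which the protocol leaves room for but does not provide for. Analyst blinding and an SAP written before follow-up are partial safeguards: an analyst blind to arm labels can still see which model has the smaller p-value. The protocol also reports that "Follow-up of participants for assessment of the primary and secondary outcomes at 24 months post-intervention is almost complete", but this does not show that the SAP was late.
- *Baseline IPV enters only if it differs significantly.* No test or threshold is stated.
- *A large gain in precision is certain.* An 11–17% fall in SE with 90–93% power at correlations of 0.32–0.44 requires group effects almost perfectly correlated across interviews some 29 months apart. Moreover, these are cluster-level results. In the planned logistic model adjustment raises power but makes the odds ratio conditional, and its SE need not shrink.
- *Chance imbalance biases the estimate.* The 95% range of the baseline difference is about ±5.6 points (1.96 × √[2×0.27×0.73×1.38/660] = 1.96 × 0.0287). That is sampling error already contained in the unadjusted SE, not an extra bias.

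**Conclusion.** The point holds as a weakness in efficiency and specification. The written criterion for adjustment is the wrong one, and the protocol does not commit to its most natural covariate. Under the stated assumptions (27% prevalence, 18 analysed per group, ICC 0.02, 30% reduction), fixed adjustment adds roughly 0–5 points to a power of about 82% at r = 0.2, 1–8 at 0.3 and 4–11 at 0.4. A gain of consequence needs r of about 0.3–0.4 or some stability of group effects over time; with r = 0.2 and no such stability it is negligible. An imbalance trigger would forgo nearly all of it. That the baseline measure predicts follow-up is a reasonable expectation, not something the documents show. No error of validity is established.

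**What to change.** In Statistical methods, replace the adjustment phrase with: *the primary model will always include the woman's baseline past-12-month physical and/or sexual IPV (yes / no / no partner or missing), whatever the observed imbalance; any further covariates are named on prognostic grounds before unblinding; the unadjusted model is reported as a supplement.* The SAP should carry the same rule.

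The cost is one sentence and no new data. With follow-up nearly complete and analysis still to come when the protocol was written, the change was still possible at that stage. The small downside is that the odds ratio becomes conditional on baseline IPV, so standardised prevalences by arm should be reported beside it.

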**Safety monitoring**

Given that no outcome data (i.e. experiences of IPV) are collected during the five-month intervention period or during the period up to 24 months post-intervention, a data monitoring committee has not been established as no interim analyses are planned. The study is being conducted following the WHO’s guidelines on researching violence against women [15]. Female interviewers for the quantitative baseline and follow-up interviews and for the qualitative IDIs have received training in interviewing techniques, gender issues, violence and ethical issues related to research on IPV. It is anticipated that any harm to women as a result of taking part in the study will be minimal. All participants are provided with information about organizations offering support to women (and their children, if appropriate) experiencing violence and other forms of abuse. Participants who report violence and other forms of abuse are offered counseling by a trained member of the study team and referral to an appropriate organization for ongoing support.

**Auditing**

Regular audits of the conduct of the study are carried out by members of the study team. These include checks that participant informed consent procedures have been followed correctly, observation and assessments of facilitation of the MAISHA curriculum sessions, and monitoring of participant attendance at MAISHA curriculum sessions and follow-up of non-attenders.

**Informed consent**

Once a microfinance loan group is identified as meeting eligibility, the study team attends the weekly meetings to present information about the study and provides a copy of the participant information sheet (see: Additional File 1) to each of the microfinance loan group members. Each microfinance loan group member meets with a member of the study team to go through the participant information sheet in detail and to allow the microfinance loan group member to ask questions about the study. If the woman agrees to participate and has demonstrated that she understands the study procedures, she is invited to sign the consent form (see: Additional File 1). Participants and key informants who are invited to take part in IDIs are given a participant information sheet providing information about the IDI (see: Additional File 2). A member of the study team meets with the participant/key informant to go through the participant information sheet in detail and to allow the participant to ask any questions. If the participant/key informant agrees to participate in the IDI she/he is invited to sign a consent form (see: Additional File 2). Participants who are invited to take part in an FGD are given an information sheet about the FGD (see: Additional File 3) following the same procedures described above for obtaining informed consent.

**Confidentiality**

Participants’ names and any information that could identify them is kept confidential. Women are allocated a unique study number. The questionnaires for the quantitative baseline and follow-up interviews are anonymous and responses to questions are entered directly onto a tablet computer. On the same day as the interview, data are uploaded to the secure study database and removed from the tablet computer before the next interview is conducted. Qualitative IDIs are audio recorded with the participant’s consent. The recordings are labelled with the study number only and are destroyed once the recording has been transcribed and translated to English. All identifiers will be destroyed at the end of the study.

**Ancillary and post-trial care**

During the 24-month follow-up period following delivery of the intervention, the study team maintains regular contact with participants in order to minimize losses to follow-up. Women who report violence and other forms of abuse during this time are offered support and referred to appropriate organizations for ongoing support post-study.

**Protocol amendments**

Since the start of recruitment, there has been one amendment to the protocol approved by the ethics committees. The follow-up period has been extended from 12 months post-intervention to 24 months post-intervention following confirmation of the additional funding required. The study investigators felt that this would be a more appropriate time point at which to assess the effectiveness of the MAISHA curriculum in reducing women’s experience of IPV, and to ensure greater comparability with the IMAGE study. In addition, the secondary outcomes were reviewed and amended to ensure that they were clearly defined, specific and measurable.

